## Abstract

**Background:**

Access to and utilization of adolescent sexual and reproductive health (ASRH) services remains poor. ASRH services in Kenya are primarily offered in health facilities and include counselling, information, and services on family planning, sexually transmitted infections, and HIV and basic life skills. The Ministry of Education also provides age-appropriate sexual and reproductive health information in schools. This paper presents a study protocol that will evaluate the effectiveness of a combined approach toward improving utilization of ASRH services.

**Methods:**

This will be a quasi-experimental study utilizing qualitative and quantitative methods. During the formative phase, data will be collected through focus group discussions, in-depth interviews, and key informant interviews to explore the barriers and facilitators of provision and utilization of ASRH services. A quantitative design will be used to obtain baseline and endline data through household surveys and client exit interviews. Following the formative and baseline household and client exit assessments, an intervention focusing on provision of ASRH service package targeting boys and girls will be implemented for 18 months. The package will include contextualized ASRH services, including counselling and age-appropriate, comprehensive sexual education for behavior change with an aim to increase utilization of ASRH services. An analysis of the primary outcome (utilization of ASRH services) will be undertaken to establish the difference in difference between the control and intervention arm, before the intervention (using the baseline survey data) and after the intervention (using the endline survey data).

**Discussion:**

Adolescents have now been included in the World Health Organization’s *Global strategy for women’s, children’s and adolescents’ health* (2016–2030), acknowledging the unique health challenges facing young people and their pivotal role as drivers of change in the post-2015 era. This study will generate evidence on whether a combined school, facility, and community approach works toward improving utilization of ASRH services. The information generated from the study will be beneficial for programming as it will identify underlying reasons for low utilization of ASRH services. Results will help to shape ASRH programs and reduce teenage pregnancy within Kenya and other similar low middle-income countries.

**Trial registration:**

The study is registered at http://www.pactr.org/, registration number PACTR201906738029948.

## Plain English summary

Pregnancy among girls aged 10–19 years is a problem in Kenya. While there are sexual and reproductive health services in place, adolescents’ access and use of these services remain very low. The Ministry of Health has developed four ways to promote the delivery of sexual and reproductive health services to adolescents. These include promoting adolescent access to services within community settings, health facilities, schools, and through digital platforms. We present a study protocol that will establish how this model can best reach the adolescents in two districts with a high burden of teenage pregnancies. The 18-month study will be implemented in two phases. The first phase will be to find out how aware adolescent boys and girls are of the available sexual and reproductive health services, what makes it difficult for them to use these services, and what needs to be done to improve their ability to use the services. Based on the information gathered, we will implement an intervention for 18 months that will establish the effectiveness of the model developed by the Ministry of Health in increasing adolescents’ utilization of sexual and reproductive health services. The information gathered from this study will be useful in shaping programs that aim to address adolescent sexual and reproductive health in Kenya and other developing countries.

## Background

The World Health Organization defines “adolescents” as individuals in 10–19 years old and “youth” as 15–24 years old [1]. Together, adolescents and youth are referred to as young people, encompassing the ages of 10–24 years. There is a gap in adolescents’ access to sexual and reproductive health (SRH) services and information, which has not been fully addressed. Several studies have assessed what works to increase access and utilization for SRH among young people. There is, however, a lack of scientifically sound data on the effectiveness of services that target young people in sub-Saharan Africa, especially in comparison to the magnitude of adolescent SRH (ASRH) challenges in the region [2]. Systematic reviews of available published literature suggest that current interventions targeting youth tend to have significant positive effects on improving their knowledge, and sometimes attitudes, regarding sexual behavior, but are less effective in demonstrating change in sexual behavior outcomes [3]. A review of best practices used in ASRH programs established that many ASRH interventions are implemented in an uncoordinated and piecemeal fashion, hence, they do not result in positive outcomes for adolescents [3].

Kenya has poor ASRH indicators. Adolescent pregnancy is a major problem in Kenya, with a teenage pregnancy rate of 18%, and an unmet need of family planning (FP)—as measured by the contraceptive prevalence rate among sexually active, unmarried girls aged 15–19 years—of 49% [4]. It is estimated that about 13,000 girls drop out of school annually in Kenya due to early and unintended pregnancy [5]. Adolescent pregnancy also increases the risk of maternal and newborn deaths and disability, including from complications from unsafe abortion, prolonged labor, childbirth, and the postnatal period [6].

To address the poor indicators, in 2015, Kenya launched a National Adolescent Sexual and Reproductive Health Policy, which provides guidance to government ministries and partners on how to respond to ASRH needs [7]. The policy advocates for the ministries of education and health, other line ministries, the political administration, and other stakeholders for successful ASRH programs and to ensure participation of young people. In addition, it recognizes the importance of addressing ASRH needs to achieve Kenya’s development goals. Despite this legal framework, implementation of ASRH services has been weak and uncoordinated. The absence of reinforcement of ASRH policies enables administrators and service providers to impose restrictions based on their personal beliefs that prohibit youth from gaining access to essential information and services. In addition, there is limited evidence to support the effectiveness of initiatives that simply provide “adolescent friendliness” training for health workers [2]*.* A study of young people’s perception of ASRH services in Kenya showed that young people wished to see an increase in ASRH services, especially in rural areas, including the use of mobile clinics [8]. The study also suggested the need to increase awareness of available ASRH services among young people and the community in general through outreach activities in the community, schools, and churches.

The Kenyan Ministry of Health has outlined four service delivery models for ASRH interventions: a) *community based (outreach services):* services and information are offered to adolescents within the community/non-medical settings; b) *clinic based:* services and information are offered to adolescent within/based in health facilities c) *school based*: services and information are offered to adolescents within the school setting; and d) *virtual based*: services and information are offered to adolescents within the virtual space or on digital platforms [4]. Implementation of this combined model has not been fully implemented and its effectiveness has not yet been established in Kenya. We present a protocol to evaluate the effectiveness of this model in Kisumu and Kakamega counties, which have some of the highest burden of teen pregnancy in Kenya, at 22 and 15% consecutively [9].

## Objectives

The primary objective of this outcome evaluation is to establish the effectiveness of a customized combined model in improving utilization of SRH services among adolescents aged 15–19 years.

The specific objectives are to:
Establish the barriers to and facilitators of ASRH use by consulting adolescents, health workers, communities, and decision makersAssess the level of knowledge, attitude, practices, and healthcare seeking behavior of adolescents toward ASRH servicesDetermine the effectiveness of a customized combined ASRH intervention model in improving utilization of ASRH services

## Methods

### Study setting

The study will be conducted in Kisumu and Kakamega counties, which are neighboring counties in western Kenya. Kisumu County is 342 km from Nairobi, Kenya’s capital city while Kakamega is 360 km from Nairobi. The total population of Kakamega is estimated to be 1,975,603 and Kisumu 1,212,956 with one in four people being an adolescent in both counties. Kakamega is the second most populous county in Kenya, with a high burden of teen pregnancy at 19%; Kisumu’s teenage pregnancy rate stands at 15%, the national average is 18% [9].

### Study design

This will be an 18-month mixed method, quasi-experimental study designed to evaluate the ASRH program’s interventions on the effectiveness of the combined model to improve utilization of ASRH services. Using a qualitative design, data will be collected through focus group discussions (FGDs), in-depth interviews, and key informant interviews. The participants will be purposively selected. Further, we will use exit interviews to study satisfaction among males and females 15–19 years of age who have received ASRH services from health facilities and outreaches (quantitative design). A quasi-experimental design with intervention and control groups will be employed, using a quantitative design to evaluate the effectiveness of the intervention on utilization of ASRH services.

### Study unit inclusion criteria and selection

Kisumu and Kakamega counties were selected as project areas in part because they are among the counties with the highest burden of teen pregnancy in Kenya—at 15 and 19%, respectively [9]. The study will focus on two sub-counties within Kisumu County (Nyando and Kisumu East) and two sub-counties within Kakamega County (Matungu and Navakholo). Within the identified four sub-counties, two wards have been selected in each sub-county, one as intervention (Kobura in Kisumu and Kholera in Kakamega) and the others as control (Bunyala West in Kisumu and Kajulu in Kakamega). The selection of the intervention ward is based on the poor reproductive and maternal health indicators coupled with low utilization of FP services among adolescents [9]. The wards were selected by the study team in collaboration with Ministry of Health officials after reviewing the wards’ service statistics. The intervention-comparison wards were selected to be similar with respect to sociodemographic characteristics and low utilization of FP services.

### Study population

Participants for the qualitative phase of the study will be drawn among adolescents, community members, teachers, healthcare workers, and county health managers in the two counties in the intervention area only, as the findings will be used to shape the intervention. Study participants for the quantitative phase of the study will be adolescents aged 15–19 years. The client exit interviews will target boys and girls aged 15–19 years, who have received any ASRH service at a facility or outreach point. The household survey will target girls aged 15–19 years old who haven’t had their first birth. This is because the unit of measure will be utilization of ASRH services, specifically the use of FP services for primary prevention of pregnancy.

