### Study eligibility criteria

Adolescent boys and girls aged 15–19 years:

• Living, at the time of the survey, in the study sites

• Voluntarily provides informed consent (emancipated minors/adolescents aged 18 and 19 years)

• Voluntarily provides assent coupled with parental permission for minors

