#### Phase 2: quasi-experimental design

A quasi-experimental evaluation design is proposed to evaluate the rollout of the ASRH program intervention to determine the effectiveness of a combined model to improve utilization of ASRH services. In both counties, program intervention and comparison groups will be selected, while taking measures to ensure that the comparison group matches the program intervention group in general composition, such as possession of similar sociodemographic characteristics. Using the stratified cluster sampling approach, a pre-intervention and post-intervention household survey will be conducted in the two study arms targeting adolescent girls at baseline and endline. The aim of the survey will be to establish the status of adolescents’ knowledge, attitude, and utilization of ASRH services, primarily FP. Implementation of the program intervention will be population-based, targeting adolescent boys and girls aged 15–19 years in the intervention areas. An analysis of the primary outcome (utilization of FP services) will be undertaken to establish the difference in difference between the control and intervention arm, before the intervention (using the baseline survey data) and after the intervention (using the endline survey data).

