In the comparison group, implementation of ASRH services will continue in the same manner as they are routinely or currently being implemented through health facilities. Health workers will be trained to provide adolescent-friendly services. An endline assessment will be done at the end of the 18 months’ implementation period. The table below presents a summary of the package of interventions that will be done in the two study arms.

The Table 2 presents a summary of the package of interventions that will be carried out in the two study arms.

**Table 2 Tab2:** Summary of package of activities by evaluation group

	Program intervention group	Comparison group
ASRH service delivery at facility level	✓	✓
ASRH service delivery at community level	✓	✗
ASRH service delivery in schools	✓	✗
Targeted social behavior change communication	✓	✗

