### Study outcomes

Our primary outcome will be FP utilization among adolescents as defined as follows:

• *Number of sexually active girls reporting use of modern contraceptive methods*

• *Number of sexually active adolescents aged 15–19 years sampled*

Sexually active girls will be defined as those who report ever having sexual intercourse. Other secondary outcomes will be knowledge and attitude on the use of modern contraception, among others as outlined in Table 3.

**Table 3 Tab3:** Study outcomes

Other study outcomes among 15–19 years		
Knowledge	Attitude	Practice/utilization
Risks faced by adolescents in pregnancy/childbirth	Toward contraceptives	Utilization of FP services
Available methods of FP	Toward ASRH services offered in facilities/communities/schools	Sexual experience – delay in age at first sex
Secondary study outcomes among 15–19 years: Reduced teenage pregnancy rates in intervention group		

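### As described, the household survey cannot support the teenage-pregnancy outcome: it leaves out girls who have given birth, and no other source is described

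*Protocol article*

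**What the plan says.** - Survey population (Protocol article, Study population): "The household survey will target girls aged 15–19 years old who haven’t had their first birth". The reason given is that the measure is utilization, "specifically the use of FP services for primary prevention of pregnancy".
- Outcome (Study outcomes, Table 3): "Secondary study outcomes among 15–19 years: Reduced teenage pregnancy rates in intervention group". No data source is attached to it.
- Timing (Phase 2: quasi-experimental design): "a pre-intervention and post-intervention household survey will be conducted in the two study arms targeting adolescent girls at baseline and endline". Description of intervention adds: "An endline assessment will be done at the end of the 18 months’ implementation period".
- Eligibility (Study eligibility criteria): residence, consent, and assent with parental permission. The residence item reads "Living, at the time of the survey, in the study sites". The list carries no restriction on prior births.
- Other quantitative data: client exit interviews reach only adolescents who have received a service, and they address satisfaction and service quality. The facility data work in both arms concerns how ASRH activities are documented. Neither is described as measuring pregnancy.

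**The concern.** A teenage pregnancy rate normally counts girls who have already given birth as well as those now pregnant. The only population-based survey in the design removes the first group, at both rounds, from numerator and denominator alike. A girl who conceives early in the intervention has delivered by endline and is no longer eligible.

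The part of the rate that stays visible is also not a neutral sample of the whole. An arm in which more girls conceive early loses more of its higher-risk girls before endline, which may lower its visible rate. A null or favourable result could then reflect who was left to interview. The Discussion expects the study to contribute to fewer teenage pregnancies in both counties, so a result on this row of Table 3 is likely to be quoted.

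**Working it through.** The plan gives no rate, effect size or sample size for the pregnancy outcome, so there is no figure of its own to reproduce. The household sample was sized on contraceptive use and is not in question here.

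**1. What the survey can see.** Setting Study population beside Table 3:
- current first pregnancy: visible;
- pregnancy that did not end in a birth, in a girl with no birth: visible if asked;
- pregnancy that ended in a birth: not visible, because the girl is ineligible.

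**2. Share lost during the intervention.** Inputs: 18 months to endline (protocol); about 9 months' gestation and a constant conception rate (assumptions). Pregnancies that go to birth and were conceived in months 0–9 have ended by month 18. Share invisible = 9 / 18 = 0.5.

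**3. Illustration with the protocol's county rates.** Let r be the teenage pregnancy rate, counting girls who have delivered or are pregnant, and s the share of those girls who have already delivered. The protocol does not give s; 60–90% is assumed.
- Dropped from the survey = r × s
- Visible rate among those left = r(1 − s) / (1 − r × s)

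| r | Dropped, s = 0.6 to 0.9 | Visible rate, s = 0.6 to 0.9 |
|---|---|---|
| 15% | 9.0% to 13.5% | 6.6% to 1.7% |
| 19% | 11.4% to 17.1% | 8.6% to 2.3% |
| 22% | 13.2% to 19.8% | 10.1% to 2.7% |

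Example: r = 0.15 and s = 0.6 give 0.09 dropped and 0.06 / 0.91 = 0.066 visible. All three rates are shown because Background gives 22% and 15% for the two counties, while Methods gives 15% and 19%.

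**4. Side effect on the primary contrast.** Let c be true contraceptive use, and bn and bu the probabilities that a non-user and a user give birth before endline. Use seen among girls without a birth = c(1 − bu) / [c(1 − bu) + (1 − c)(1 − bn)]. The planning rate for contraceptive use is not stated, so a low and a middling level are tried, each with a true difference of 15 points.

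| bn, bu | Seen difference, 18% v 33% | Seen difference, 49% v 64% |
|---|---|---|
| 0.10, 0.02 | 15.6 points | 14.8 points |
| 0.20, 0.03 | 16.4 points | 14.5 points |
| 0.30, 0.05 | 17.1 points | 14.1 points |

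Example: for 18%, 0.1764 / 0.9144 = 0.193; for 33%, 0.3234 / 0.9264 = 0.349; difference 0.156. Over the grid the shift runs from 0.9 points down to 2.1 points up.

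**The case against.** The restriction is deliberate and reasoned: the study wants contraceptive use for preventing a first pregnancy, and girls without a birth are the right group for that. Pregnancy is not in the objectives, the stated hypothesis or the sample size; it is one row of Table 3. An article may also leave the source of a secondary outcome to the full protocol, and this study does use routine statistics elsewhere, for choosing wards and for sizing the survey. These points stand as limits on the claim. They do not remove the conflict. The reason given supports the contraceptive-use measure and not a pregnancy rate from the same sample, and no analysis plan can recover girls whom eligibility kept out.

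Three stronger readings are tempting, and the document does not support them.

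- *A reader might infer that pregnancy cannot be measured at all.* Current first pregnancies and losses remain observable, and a source not described in the article may exist. What the survey as described cannot give is a rate that includes births.
- *A reader might infer that the primary result is seriously biased, because the intervention affects who stays eligible.* The mechanism is real, and applying the same rule at baseline does not cancel it if births change. But the shift is about 1–2 points, its direction depends on an unstated level of use, and the calculation follows a closed group whereas the design is repeated cross-sections. For girls without a birth, the population the plan chose, the level of use in each arm is not overstated; only a change in composition remains.
- *A reader might extend this to the primary denominator*, since "Sexually active girls will be defined as those who report ever having sexual intercourse" and Table 3 also lists "delay in age at first sex" as an outcome. Contraceptive use among sexually active girls is a reasonable measure, and the document gives nothing from which to size such an effect.

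**Conclusion.** The point holds as a mismatch between the survey population and a listed secondary outcome. About half of the intervention-period pregnancies that end in a birth are invisible at endline, given a constant conception rate and nine months' gestation. With the county rates in the protocol, and 60–90% of counted girls already delivered, the survey drops roughly 9–20% of girls and sees a rate of about 2–10% in the rest. A reduction in teenage pregnancy rates cannot be concluded from that. The primary difference-in-differences is little affected and does not need redesign. Separately, Study eligibility criteria omits a restriction that Study population imposes.

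**What to change.** 1. For the pregnancy outcome only, also admit girls aged 15–19 whose first birth fell within the 18 months before the survey round. Use the same look-back at baseline if that round has not been fielded.
2. Record pregnancy and birth dates, and compute the rate on all these girls. The dates matter because births in about the first nine months of the look-back were conceived before it opened.
3. Keep the primary difference-in-differences in girls without a first birth, as planned. Add a sensitivity analysis that includes the recent mothers. Do not replace the baseline-adjusted analysis with an endline-only comparison: wards were not randomised, and the intervention wards were chosen for poor indicators.
4. If eligibility cannot change, redefine the outcome as current first pregnancy among girls without a birth, or remove teenage pregnancy as an outcome. If a separate source is intended, name it.
5. Align Study eligibility criteria with Study population.

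Cost: a protocol amendment, a few birth-history questions, and a small number of additional or substituted interviews. Additional interviews are preferable, since substitution takes from the number planned for the primary outcome.

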### Sampling

#### Qualitative study

In-depth interviews will be done among adolescents, teachers, healthcare workers, and community representatives while key informant interviews will be done with the county leadership. FGDs, comprising of sessions with only boys, only girls, and a mix of both will also be held. A total of 116 participants will be selected purposefully to participate in the study (Table 1).

**Table 1 Tab1:** Formative assessment sample sizes in the ASRH intervention group, Kisumu and Kakamega counties

Participant group	Approach/Method	Description of participants	# per ward	Fre- quency	Total	Focus of the interview/FGD
Adolescents age 15–19 years	IDI (12)	3 boys and 3 girls	6	2	12	To assess adolescents’ barriers, experiences, and preferences around use of ASRH services
	FGD (6)	Girls FGD (10) Boys FGD (10) Mixed FGD (5 boys and 5 girls)	30	2	60	To assess adolescents’ barriers, experiences, and preferences around use of ASRH services
Teachers	IDI (12)	3 male and 3 female	6	2	12	To explore teachers attitudes toward providing ASRH information and services to adolescents within school; personal beliefs, policy direction toward ASRH service provision in schools, and school re-entry post pregnancy; and adaptability to meet adolescent’s health needs
Community representatives	IDI (12)	Chief, Village elder, parent, youth champion, religious leader, ward administrator, police (Officer Commanding Police Division—OCPD), community health worker	6	2	12	To explore the decision-making processes around adolescent’s sexuality and use of ASRH services, gender roles, and personal beliefs, gender-based violence against adolescents, legal issues (if any)
Health workers	IDI (10)	Representatives from public health facilities: dispensary or health center and sub-county hospital; chemist/pharmacy attendant; and private facility	5	2	10	To explore health workers experiences in providing ASRH services to adolescents
County leadership	KII (10)	County directors— health, youth, education, reproductive health coordinator; high school head teacher, primary school head teacher	5	2	10	To establish the existence of policies supporting provision of ASRH information and services in various settings and level of implementation
Transcripts	62	Total participants			116	

*IDI* in-depth interview, *FGD* focus group discussion, *KII* key informant interview

